### Measurements

#### Survey instrument (conducted at baseline, 6, 12, and 18 months)

The instrument incorporates common measures developed by the NIDA Harm Reduction Research Network, (37) measures from a prior data harmonization effort for OPC measures, [37] and previous work conducted by the study team. [38–41] In addition, the instrument underwent multiple rounds of review and cognitive testing by our partners at the OPCs and SSP partner organizations, including service staff and participants. A summary of our measures is provided in Table 1 and our baseline instrument is included in the Appendix. Participants receive $40 for each completed baseline and follow-up survey.

**Table 1 Tab1:** Domains and corresponding items measured in baseline and follow-up surveys given to study participants

Domain	Items
*Primary Exposures*	
OPC use	In the past 30 days: used an OPC, name of OPCs used, frequency of use, proportion of drug use consumed at OPC
*Primary Outcomes*	
Overdose	Lifetime and past 30-day nonfatal overdose
Hepatitis C	Lifetime and past 6-month hepatitis C test result, past 6-month positive hepatitis C diagnosis, receipt of treatment
HIV	Lifetime and past 6-month HIV test result, past 6-month positive HIV diagnosis, receipt of ARV and PrEP
Other infections	Past 6-month skin and soft tissue infections, mode of treatment for infection, past 6-month diagnosis of endocarditis
Healthcare use	Past 6-month: number of times used the emergency room to access health care; number of nights spent in the hospital
Harm reduction service use	Year and month of first use; type of services used and frequency of use in the past 3 months
Substance use disorder treatment	Past 6-month: referral to treatment; source of referral; enrollment in treatment; current status of enrollment
*Confounders*	
Drug use	Lifetime, past 30 day, and past 7 day self-reported by type of drug and mode of use
Injection practices	Past 30 days and past 7-day injection practices
Reasons for using OPC	No safe place to use, prior overdose, change in drug dealer, concern about safety of the supply
Syringe disposal	In the past 30 days, number of days: disposed of syringes in a public place; in a hazardous waste container
Demographics	Age, sex, gender identity, race and ethnicity, education
Socioeconomic status	Housing status, zip code, employment, income, money in exchange for sexual activities
Criminal legal system	Past 30 days: number of times stopped by police, arrested, held overnight in jail or prison
Health-related quality of life	Physical function, ability to participate in social roles and activities, depression, anxiety, fatigue, sleep disturbance, pain

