To be eligible for the study, participants must have used an illegal drug in the past 30 days. Further, they must be ≥ 18 years old and active clients of an OPC and/or SSP, defined as use in the past 30 days. They must be able to complete a survey in English or Spanish and provide written informed consent. Inclusion criteria for participants recruited at an OPC site also include use of the OPC service in the past 30 days. Study participants complete 60–90-min, in-person, computer-assisted surveys with a trained interviewer at baseline and months 6, 12, and 18. While initial recruitment takes place at the OPCs and SSPs, later in-person interviews take place at the OPC/SSP, at a field office, or a participant’s chosen location. In addition, they are recontacted each month (in person or by phone) during the 18-month period for a 5–10-min check-in.

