#### Check-in instrument: monthly retention visits

Each month, participants are contacted for a brief visit and asked to update their contact information. They are asked about their frequency of use and the proportion of drug use consumed at an OPC (Table 1) and about the number of times they had an overdose in the past 30 days. Participants receive $10 for each completed check-in.

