#### Calculate additional costs and cost savings to the healthcare and criminal justice systems for OPC study participants compared to non-OPC SSP study participants

To determine additional healthcare and criminal justice system savings and costs from OPC use, we will use self-reported data from Aim 1 on use of medical, social, and substance use treatment services and engagement with the criminal justice system. These data will be collected from participants in the baseline and follow-up assessments using questions from NIDA’s Seek, Test, Treat, and Retain Service Utilization Domain that details medical service utilization. [95] Self-reported data on health care encounters has been used extensively in previous research. [96, 97] Health-related quality of life measures will also be collected using the PROPr instrument to inform future cost-effectiveness analysis. [98] We will use various established sources for health care payment estimates and criminal justice costs to estimate healthcare system and criminal justice system costs. [99–102] 

Costs based on health services and criminal justice utilization will be compared between OPC and non-OPC SSP participants 6, 12, and 18 months after baseline to estimate incremental costs per participant and potential downstream cost offsets/savings resulting from OPC use. A health care system and criminal justice system cost (societal) perspective will be taken in this economic analysis. Analyses will be conducted using a generalized linear mixed model (GLMM), which allows for the inclusion of random effects and is recommended for economic analyses. [93] The method of recycled predictions will be used to obtain the final predicted mean cost values, which will be summed and tested. [93] To account for sampling uncertainty in point estimates, the *p*-values and standard errors will be estimated using nonparametric bootstrapping techniques. For the 18-month comparison, 3% discounting will be applied. [92] Using these methods, we will estimate the predicted mean value by resource, study group (e.g., OPC and non-OPC SSP) time period (6, 12, and 18 months), and geography (RI, NYC). TThe net value of OPCs will then be calculated by taking the difference between the average estimated total cost of OPCs and non-OPC SSPs to determine if the OPCs have a greater net benefit compared to non-OPCs.

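### Aim 4 costs criminal justice use by 6-month period, but the survey items in Table 1 cover only the last 30 days of each period, and no scaling or other participant-level source is described

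*Protocol article*

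**What the plan says.** The protocol article, Aim 1 (Study design), schedules "in-person, computer-assisted surveys with a trained interviewer at baseline and months 6, 12, and 18". Table 1 then gives recall windows domain by domain:

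- Criminal legal system, listed among the confounders: "Past 30 days: number of times stopped by police, arrested, held overnight in jail or prison".
- Healthcare use: "Past 6-month: number of times used the emergency room to access health care; number of nights spent in the hospital".
- Substance use disorder treatment: "Past 6-month: referral to treatment; source of referral; enrollment in treatment; current status of enrollment".

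The monthly check-in updates contact details, asks about OPC use, and asks "about the number of times they had an overdose in the past 30 days". It has no criminal justice item.

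In Aim 4, the subsection on additional costs and cost savings states: "we will use self-reported data from Aim 1 on use of medical, social, and substance use treatment services and engagement with the criminal justice system". On timing it says: "Costs based on health services and criminal justice utilization will be compared between OPC and non-OPC SSP participants 6, 12, and 18 months after baseline". Mean costs are predicted by resource, group, period and jurisdiction, and the predicted means are summed. The article does not say how a 30-day count becomes a cost for a 6-month period.

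**The concern.** The criminal legal items have a window that may suit a confounder, where recent contact with police is a reasonable marker. Aim 4 reuses the same items as a cost outcome, and there the window matters in a different way. A cost for a period needs use over that period, and these items reach only its final 30 days. The main healthcare items reach all of it.

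Criminal justice savings are one of the two components that Aim 4 sets out to estimate. If the two are added on unequal time bases, the smaller base shrinks its component and any OPC versus non-OPC difference in it. If they are first put on a common base, the criminal justice figure depends on an extrapolation from one month to six and loses precision. In neither case can the analysis recover the months that were not asked about.

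**Working it through.** The article gives no coverage or precision figure on this point, so there is none to reproduce.

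**Inputs**
- Criminal legal recall window: 30 days (Table 1).
- Window for emergency room visits, hospital nights and substance use treatment: 6 months (Table 1). Harm reduction service use is an exception at 3 months.
- Survey interval: 6 months (Aim 1, Study design), taken as 365.25/2 = 182.6 days.
- Follow-up surveys: three, over 18 months or 548 days.

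**Step 1. Share of time observed**
- Per interval: 30/182.6 = 16.4%, so 83.6% is not observed. For intervals of 180 to 184 days the observed share is 16.7% to 16.3%.
- Over follow-up: 3 × 30 = 90 days; 90/548 = 16.4%.

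**Step 2. Other sources in the article**
- The check-in has no criminal justice item.
- Table 2 links participants to health records only.
- The arrest records in Aim 2 are mapped by location and are not described as linked to participants.

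None of these fills the gap.

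**Step 3. Effect if counts enter unscaled**
- Factor: 182.6/30 = 6.09, so the component and any group difference in it are understated about 6.1-fold.
- The summed total is understated by s × (1 − 1/6.09) = s × 0.836, where s is the true criminal justice share of the total. The article gives no s. For assumed values of 10%, 30% and 50%, the total is understated by about 8%, 25% and 42%.

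**Step 4. Effect if counts are scaled by f = 6.09**
- Bias: none if the rate is constant within the interval.
- Precision, pure Poisson with mean m per 6 months: a full count has variance m. A scaled 30-day count has variance f² × (m/f) = f × m. The variance ratio is 6.09, and the standard error ratio is √6.09 = 2.47.
- Precision, if people differ persistently in their rates: let the between-person variance of the 6-month rate be v × m. The full count has variance m(1 + v) and the scaled count m(f + v), a ratio of (f + v)/(1 + v). For an assumed v = 1 this is 7.09/2 = 3.54, a standard error ratio of 1.88. For an assumed v = 3 it is 9.09/4 = 2.27, a ratio of 1.51. The figure of 2.47 is therefore an upper value within this family.

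**Step 5. Coverage after the change**
- Check-in route: 18 × 30 = 540 of 548 days, or 98.6%, if every contact is completed.
- 6-month survey item: about the whole interval, as for the main healthcare items.

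**The case against.** **The instrument is not shown.** The article presents Table 1 as a summary and places the full survey in an appendix. For Aim 4 it adds: "These data will be collected from participants in the baseline and follow-up assessments using questions from NIDA’s Seek, Test, Treat, and Retain Service Utilization Domain". The windows of those questions are not visible, and some could be longer. This stands as a reason for medium confidence. It does not settle the matter, because the article describes that set as detailing medical service utilization, and Table 1 is the only place where it gives a criminal justice window.

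**A reader might infer that the planned analysis understates criminal justice costs sixfold.** The article does not support that. It never says that raw 30-day counts enter unscaled, and converting windows to a common period is a costing detail that a fuller plan may hold. The sixfold figure is conditional.

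**A reader might also infer that the balance between the components is wrong whichever way the counts are handled.** That does not follow either, since scaling is unbiased under a constant rate. What remains is that no scaling rule supplies the uncollected months. The constant-rate assumption also needs thought for detention: someone in custody may be harder to survey in person, and a 30-day item can record at most about 30 nights of a longer stay.

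**Short recall may be more accurate.** This is a fair point, and the Aim 3 analysis section itself names recall as a difficulty of self-report. But the same survey already asks 6-month counts for emergency room visits and hospital nights, and the check-in route keeps 30-day recall.

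**Conclusion.** The mismatch stands as the article describes the measures. The criminal legal items observe about 16% of follow-up time, the main healthcare items observe all of it, and Aim 4 costs both by the same periods.

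The consequence depends on handling. Unscaled, the criminal justice component is understated about 6.1-fold relative to healthcare. Scaled, it is unbiased only under a constant within-interval rate, with a standard error for a 6-month count up to about 2.5 times larger under Poisson counts and less under persistent differences between people.

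Two stronger statements go too far. The five-sixths left unobserved is a share of time, and it is a share of criminal justice use only if the rate is constant. The estimate also cannot be said to rest on a few rare events, because the article gives no rate for stops, arrests or detention, and the target sample is 1000.

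The change should be made, since months that pass without being asked about are hard to recover. The point touches one Aim 4 cost component and leaves the Aim 1 primary outcomes alone.

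**What to change.** First check the appendix instrument and the cited question set for a longer criminal justice window. If there is none, do one of the following:

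- **Preferred:** add number of arrests and nights held (and police stops, if they are to be costed) to the monthly check-in, which already uses 30-day recall.
- **Alternative:** add a past-6-month item to the follow-up surveys and keep the 30-day item for confounder adjustment.

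For intervals already collected, and for missed check-ins, scale by days covered, state the constant-rate assumption, and carry the added uncertainty into the planned bootstrap.

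The cost is one or two items in a 5–10-minute contact, by minor amendment, with slight participant burden. Check-in coverage will be incomplete where contacts are missed, possibly more often for people in custody. The 6-month item trades better coverage for more recall error.

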#### Check-in instrument: monthly retention visits

Each month, participants are contacted for a brief visit and asked to update their contact information. They are asked about their frequency of use and the proportion of drug use consumed at an OPC (Table 1) and about the number of times they had an overdose in the past 30 days. Participants receive $10 for each completed check-in.

#### Outcomes measured through administrative health records

To provide a comprehensive assessment of change in health conditions associated with OPC use, we complement self-reports with administrative health records. Participant identifiers will link participants to their administrative health records. Table 2 presents the sources and types of information we plan to collect, leveraging our partnerships with the NYC Department of Health and Mental Hygiene (DOHMH), NYS Office of Addiction Services and Supports (OASAS), the RI Department of Behavioral Health, Developmental Disabilities, and Hospitals (BHDDH), and the Rhode Island Department of Health (RIDOH). We link participants to their health records 18 months prior to their first survey date and for up to three years post-enrollment, to track pre- and post-OPC changes in their health using probabilistic matching with the last four digits of each participants’ social security number, first and last name, date of birth, and sex. [42] We use a minimum, common set of data sources, including Medical Examiner, Medicaid, and data from licensed substance use disorder treatment facilities (through OASAS and BHDDH), ensuring a high degree of comparability across jurisdictions. In Rhode Island, we can also link participants to prescription drug monitoring program data, as we have done in prior work. [43]

**Table 2 Tab2:** Administrative health record data sources linked with study participants

Domain	Items	NYC data^1^	Rhode Island data^2^
Fatal overdose	All drug overdose, stimulant, and opioid	Office of Chief Medical Examiner	Office of Chief Medical Examiner
Non-fatal overdose	All drug overdose, stimulant, and opioid	NYC Regional Health Information Exchange (RHIO), Statewide Planning and Research Cooperative System (SPARCS),^3^ Medicaid	Emergency medical services data, Medicaid^4^
Drug-related health conditions	Hepatitis C, HIV, skin and soft-tissue infections, infective endocarditis	NYC RHIO, SPARCS, and Medicaid	Medicaid^4^
Emergency department visits	Overall ED use, drug-related emergency department (ED) visits	NYC RHIO, SPARCS, and Medicaid	Medicaid^4^
Substance use disorder treatment	Initiation in a licensed treatment program, including medications for OUD	OASAS and Medicaid	Prescription drug monitoring program, BHDDH, and Medicaid

^1^Available through DOHMH; ^2^Data already available through data use agreements for R01DA046620; ^3^SPARCS is a comprehensive all payer data reporting system for New York State; ^4^Medicaid covers 88% of the study target population in RI and 75% of the target population in NYC

#### Analyses

We use a custom instance of REDCap™ to conduct field-based surveys, which allows for direct transfer and storage of data into our institutions’ secure, HIPAA-compliant, secure computing environments.

To evaluate the effectiveness of attending OPCs on outcomes, we will conduct time-to-event and multi-state analyses. [44] Our primary outcomes will include fatal and non-fatal overdoses, injection-related infections (i.e., skin and soft tissue infections, endocarditis), emergency department use, and substance use disorder treatment initiation. We will measure these outcomes using administrative health records and survey data. Our time-updated exposures of interest will be any use of an OPC in the past month, as well as two measures of exposure “dose”: intensity of use (e.g., daily vs. non-daily) and the fraction of drug use conducted at an OPC in the past month (examined as continuous and > 50% vs. lower). All participants will be asked about OPC use regardless of recruitment source, which will permit analyses of time-varying exposures (e.g., persons recruited from an SSP with no OPC may use an OPC located at another site, which will be captured in our data).

Realizing that there are time-dependent confounders (e.g., prior SSP use), and that several of our primary outcomes are likely recurrent, we will deploy marginal structural Cox models (MSCM)(46) and multi-state marginal structural Cox models (MS-MSCM). [45, 46] MSCM and MS-MSCM allow for the estimation of the effect of time-varying treatments on a time-to-event outcome (MSCM) or recurrent, interrelated events (MS-MSCM) with time-dependent confounders. Specifically, we will estimate the marginal hazard ratio of OPC use by employing a Cox model weighted by the set of inverse probability weights (IPW) and inverse probability of censoring weights (IPCW). IPW will be used to balance confounders over time by taking the inverse of the conditional probability of OPC use, given the whole treatment histories and time-dependent and time-invariant confounders. IPCW will be used to balance confounders across censored and uncensored participants, thus dealing with informative censoring as a result of loss to follow-up. [47] We will obtain such probabilities by using pooled logistic regression models. To overcome extreme weights, we will implement stabilized IPW, truncated weights, and optimal probability weights which are based on novel techniques developed by a member of the study team. [48, 49] While other methodologies, such as G-computation, [50] can be used to estimate the effectiveness of time-varying treatments, we propose to use MSCM given their less computational demanding implementation and easier interpretation.

First, we will test the hypothesis that any use of OPC in the past month, higher intensity of use, and higher fraction of drug use conducted at an OPC are associated with a greater decline in the hazard of fatal overdose. To test these hypotheses, we will fit separate MSCM (one per type of OPC exposure), accounting for time-varying confounders, including prior history of: non-fatal overdose, substance use, healthcare use, prior harm reduction service use, and prior engagement with the criminal justice system; and time-fixed confounders (socioeconomic status, demographic characteristics) through IPWs. We will fit the same types of models for other non-recurrent outcomes, including initiation of treatment for substance use.

Second, we will test the hypothesis that OPC use (any past month use, intensity of use, fraction of drug use) is associated with lower hazard and recurrence of non-fatal overdoses, by fitting MS-MSCM. We will account for the same types of potential confounders as considered for non-recurrent outcomes. We will fit the same type of MS-MSCM models for other recurrent and interrelated outcomes, including skin and soft-tissue infections, infective endocarditis, and emergency department use.

Following the intersectional risk environment framework, [33] we will conduct intersectional analyses to determine whether primary outcomes of interest (e.g., uptake of substance use treatment) vary by intersecting social positions and identities (e.g., race, gender). We will employ intersectional methods such as stratification and inclusion of interaction terms, as appropriate. [51] More novel approaches such as multilevel analysis of individual heterogeneity and discriminatory accuracy will also be explored. [52] Finally, we will conduct exploratory stratified analyses to determine whether observed effects vary by jurisdiction (RI vs. NYC).

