## Introduction

More than 100,000 people died of an overdose in 2022 in the United States. The age-adjusted rate of overdose deaths almost quadrupled from 2002 to 2022, making overdoses one of the leading causes of injury death in adults. [1] Fentanyl and other illegally manufactured synthetic opioids drive overdoses and have contributed to historically high levels of death from overdose since 2014, starting in the East Coast and shifting to the West Coast in more recent years. This crisis has coincided with rapidly rising rates of hepatitis C virus infection, HIV outbreaks, and other sequelae of unsterile drug use. [2–4] The economic cost of the crisis exceeds $1 trillion annually. [5]

Persistently high levels of overdose in the United States have led to a call for new solutions. Overdose prevention centers (OPCs) have been proposed as a strategy to reduce drug-related harms in the context of a volatile illegal market dominated by highly lethal products. OPCs (also known as supervised consumption sites, safe injection facilities, drug consumption rooms, or harm reduction centers) are community-based facilities at which clients consume pre-obtained controlled substances under the supervision of personnel trained to intervene in the event of an overdose. [6] In most countries, OPCs resemble community health clinics, with booths that permit supervision by trained personnel. OPC staff also provide education about safer drug consumption practices, access to sterile supplies, referrals to other treatment, health, and recovery services. While OPCs have long been in operation in other countries, no publicly recognized OPCs existed in the United States before 2021. In July 2021, Rhode Island (RI) became the first state to authorize OPCs through legislation; the first OPC service will open in Fall 2024. [7] In November 2021, the first two publicly recognized OPCs in the US opened in New York City (NYC). [8–10]

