The Study Assessing the Effectiveness of Overdose Prevention Centers Through Evaluation Research (SAFER) aims to evaluate the effectiveness of the NYC and RI OPCs by conducting a parallel, multi-method, individual- and community-level evaluation of OPCs in NYC and RI in 2023–2027. By evaluating OPCs in these distinct contexts, SAFER intends to determine the generalizability of OPC effectiveness across diverse settings. The study aims include:*Identify individual health outcomes of OPC use* by investigating whether people who attend OPCs experience lower rates of fatal and non-fatal overdoses, drug-related health problems (e.g., skin & soft tissue infections), emergency department use, and a higher rate of initiating evidence-based treatment for substance use disorders, compared to people who use drugs and attend SSPs with no OPC.*Examine the community impact of OPCs* by determining whether census block groups surrounding OPCs experience a greater change in public health conditions (e.g., fatal and non-fatal overdoses), public disorder (e.g., drug-related litter, arrests, noise complaints), and acute economic conditions (e.g., property values) relative to a comparison set of census block groups unexposed to OPCs.*Investigate how operational contexts, program models, and operating procedures* shape how people who use drugs use OPCs and explore their impact on overdose vulnerability and other drug-related health outcomes, using qualitative and ethnographic methods.*Estimate OPC costs and potential cost savings to the healthcare and criminal justice systems associated with OPC use*, to support future estimation of longer-term cost and health outcomes.

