### Aim 1: Individual health and treatment outcomes associated with OPC use among PWUD

#### Study design

While a randomized controlled trial (RCT) would be the gold standard for OPC evaluation, community and political factors that drive the timing of OPC service openings make randomization unfeasible, and RCTs of OPCs have previously been deemed unethical due to a lack of equipoise. [35] Hence, we use a quasi-experimental, pre-/post-intervention design with a comparison group, [36] to test whether individuals who use an OPC experience greater changes in the outcomes of interest than individuals who do not use an OPC. We recruit participants from two types of organizations that serve similar populations, facilitating group comparability by level of OPC use: (1) harm reduction organizations that provide OPC services (two sites in NYC) or plan to provide OPC services (one site in RI); and (2) a comparison set of SSPs with no plans to open an OPC (five organizations in NYC and three in RI). The target sample is 250 in each arm per jurisdiction, so that we recruit 500 participants in NYC and 500 in RI (N = 1000 total). Target numbers per site are proportional to the client population served by each organization. We collect pre- and post-OPC data from all study participants, including administrative health records and survey data, as described below.

We use venue-based recruitment for two reasons. First, this ensures that all groups represent a comparable underlying population of individuals already connected to a harm reduction service provider. Second, this permits us to compare populations that receive harm reduction services (e.g., syringe exchange, naloxone), so we can isolate the effect of OPC use on outcomes.

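### The Aim 1 Cox models name neither calendar time nor jurisdiction, although the Rhode Island OPC cannot be used before Fall 2024, so a background trend can pass partly for an OPC effect

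*Protocol article*

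**What the plan says.** All references are to the protocol article.

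- **Timing.** The Introduction describes an "individual- and community-level evaluation of OPCs in NYC and RI in 2023–2027". For RI it says that "the first OPC service will open in Fall 2024". The NYC OPCs opened in November 2021, before the study starts.
- **Recruitment (Aim 1, Study design).** Sites provide OPC services "or plan to provide OPC services (one site in RI"). The design is pre-/post-intervention with a comparison group: "We collect pre- and post-OPC data from all study participants", covering both records and surveys. The eligibility paragraph of the same section requires anyone recruited at an OPC site to have used the OPC in the past 30 days. It sets no such condition for SSP recruits.
- **Record linkage (Outcomes measured through administrative health records).** Linkage runs from 18 months before the first survey to three years after enrolment.
- **Exposure (Aim 1, Analyses).** "Our time-updated exposures of interest will be any use of an OPC in the past month", plus two dose measures.
- **Adjustment (Aim 1, Analyses).** The weighted Cox models are described as "accounting for time-varying confounders, including prior history of: non-fatal overdose, substance use, healthcare use", then harm reduction and criminal justice history, with socioeconomic status and demographics as time-fixed confounders. Neither calendar time nor jurisdiction is named. Jurisdiction appears only in exploratory stratified analyses of effect variation.

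The article states neither the Cox time axis and its origin nor whether pre-opening or pre-enrolment time enters the risk sets.

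**The concern.** Use of the RI OPC is impossible before Fall 2024. Under the exposure definition, any RI month before then is a month without use of that OPC. RI exposed time therefore lies wholly after opening, while RI unexposed time may lie on either side of it. If the two sets of months differ in average calendar date and the model does not hold calendar time fixed, a change in background risk enters the hazard ratio. A falling background looks like benefit and a rising one like harm.

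The eligibility rule offers a second route to the same problem. RI OPC-site recruits can enter only after opening, while RI SSP recruits face no such limit, so the two arms may cover different calendar periods.

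The planned weights do not repair this by themselves. A weight model without calendar period or opening status cannot know that exposure was impossible in the early RI months, and may give them a positive probability. Stabilising or truncating the weights does not change that.

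The article itself reports overdose deaths almost quadrupling from 2002 to 2022 and shifting between regions, so a flat background cannot be presumed in a policy-relevant evaluation.

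**Working it through.** **Stated figures.** The article gives no power, event count or bias figure for Aim 1, so there is nothing to reproduce beyond 2 arms × 2 jurisdictions × 250 = 1000.

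**Inputs from the article.** 250 per arm per jurisdiction; 18 months of survey follow-up; 18 months of record lookback; RI opening in Fall 2024; NYC already open. A near-quadrupling over 20 years is at most 4^(1/20) = 1.072, about +7% a year on average. The trend for 2023–2027 is not given.

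**Assumptions.** True hazard ratio 1; the same background hazard in both jurisdictions; trend between −20% and +20% a year; opening on 1 October 2024; NYC arms enrolling together from July 2023 to June 2024; OPC-arm members always exposed once their OPC is open, SSP-arm members never. Three RI enrolment calendars:

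- A: SSP arm January–December 2024, OPC arm January–December 2025.
- B: both arms January–December 2025.
- C: both arms January–September 2024, before opening.

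**Scenario A by hand (follow-up only, time-on-study axis).** Arms are equal in size at every follow-up month, so the hazard ratio is expected exposed events divided by expected unexposed events. Let g be the yearly factor and set the NYC hazard to 1. RI SSP enrolment is 6 months later than NYC (factor g^0.5) and RI OPC enrolment 18 months later (g^1.5).

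- RI alone: g^1.5 / g^0.5 = g. At −20% this is 0.80; at −10%, 0.90; at +10%, 1.10; at +20%, 1.20.
- Pooled: (1 + g^1.5) / (1 + g^0.5). At g = 0.8: (1 + 0.7155) / (1 + 0.8944) = 0.906. At g = 0.9: 1.8538 / 1.9487 = 0.951. At g = 1.1: 1.051. At g = 1.2: 1.105.

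**All scenarios.** Solving the expected Cox partial-likelihood score on a monthly grid gives these hazard ratios at −20% / +20% a year:

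| RI enrolment | RI, follow-up only, time on study | Pooled, same, unstratified | RI, lookback added, time on study | RI, lookback added, no time axis |
|---|---|---|---|---|
| A | 0.800 / 1.200 | 0.906 / 1.105 | 0.799 / 1.199 | 0.720 / 1.297 |
| B | 1.000 / 1.000 | 1.000 / 1.000 | 0.981 / 1.011 | 0.855 / 1.118 |
| C | 0.981 / 1.013 | 1.006 / 0.997 | 0.981 / 1.013 | 0.755 / 1.232 |

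The last column pools all person-time without a time axis. The article does not propose this; it serves as an outer bound.

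**Pre-opening share of RI unexposed time, follow-up only.** A: 937.5 / (250 × 18 = 4500) person-months = 21%. B: 0%. C: 2500 / 5750 = 43%. With lookback the shares are 68%, 42% and 78%.

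**Remedies tested.**

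- Calendar time as the axis, stratified by jurisdiction: 1.000 in every scenario and at every trend.
- Dropping RI pre-opening time only, keeping time on study and stratifying by jurisdiction: 1.000 in B and C. In A, at −20% a year, the pooled value moves only from 0.906 to 0.922, because the arms still cover different periods.
- Stratifying by jurisdiction also matters: in B with lookback, at −20% a year, the pooled time-on-study value is 1.053 unstratified and 0.993 stratified.

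**The case against.** The strongest reply is that a condensed article need not list every model term. The confounder list is open-ended, and the Cox time axis, its origin and risk-set entry are details a full plan may settle. If that plan uses calendar time stratified by jurisdiction, the bias is gone. RI also has a concurrent comparison arm of 250 whose follow-up can run alongside exposed time, and in NYC, half the planned sample, the OPCs were open before the study began. Earlier records could serve purely as baseline history.

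Much of this stands, and it rules out several stronger readings that a reader might infer:

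- That no Aim 1 model accounts for calendar time. The article only fails to name it.
- That pre-opening RI months are entered as unexposed time. This follows naturally from the exposure definition and the pre/post design, but is not written.
- That any trend is read as an OPC effect. The calculation ranges from no bias to a full year of trend in RI, and pooling with NYC roughly halves the latter.

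The reply does not remove the point. The article fixes the estimator, the weight types, the form of the weight models and the confounder classes, and gives jurisdiction an exploratory role only. It discusses positivity for Aim 2 but not for RI before opening in Aim 1. The conflict between pre-OPC survey data from everyone and recent OPC use as an entry condition lies within the article itself.

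**Conclusion.** The point holds in a limited form. The named Aim 1 adjustment leaves out calendar time and jurisdiction in a study where one jurisdiction's OPC cannot be used before Fall 2024, and the RI recruitment statements must be reconciled.

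The size depends on the RI enrolment calendar. Under an assumed 12-month stagger and an assumed trend of −20% a year, a null effect appears as 0.80 in RI and about 0.91 pooled. At the article's long-run average of about +7% a year, the RI value would be about 1.07. If both RI arms enrol together after opening and only follow-up time is used, there is no bias. If both enrol before opening on a time-on-study axis, the RI value is about 0.98 to 1.01 for trends between −20% and +20% a year. Pooling lookback time as unexposed without a time axis would be worse.

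The enrolment calendars, trends and exposure patterns are assumptions, because the article gives none of them. The calculation isolates the trend and includes no other confounding. The change is worth making because it removes this bias in every scenario at little cost.

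**What to change.** 1. Use calendar time as the Cox time axis, with entry at enrolment, or use calendar quarter as strata. Stratify the baseline hazard by jurisdiction in the main models, not only in exploratory ones.
2. Include calendar period and jurisdiction in both the exposure and the censoring weight models.
3. Fit no exposure weights to RI months before opening, when the probability of using the RI OPC is known to be zero. State whether those months enter the risk sets. On a calendar axis stratified by jurisdiction they contain no exposed person and add nothing to the hazard ratio.
4. Use records from before enrolment as baseline history only.
5. Reconcile the Study design statement on pre-OPC survey data with the OPC-use entry condition for RI, and give the enrolment period of each RI arm.

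Dropping pre-opening RI time alone is not sufficient if the arms enrol at different times.

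Cost: wording, slightly more analysis work and a small loss of precision from stratification. The loss grows if the RI arms overlap little in calendar time, because only overlapping periods then inform the RI comparison.
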